#### Ethical considerations

The study was given ethical consent on 30^th^ November 2011 Dnro 19U/2011 from the Ethics Committee of the Central Finland Health Care District. Written informed consent will be obtained from all subjects before their participation in the study. All subjects included have the right to withdraw from the study whenever without needing to provide a reason for withdrawal. The study will be conducted according to good clinical and scientific guidelines and the declaration of Helsinki (2000).

#### Assessment of side effects

Adverse effects or health problems attributable to the testing protocol or interventions exercise protocol will be documented and reported. Following each individual measurement and training session self-reported knee pain will be assessed using a visual analogue scale (VAS 0-100 mm) along with any other physical symptoms such as pain elsewhere than knee, stiffness and general fatigue. All subjects will have medical insurance and have access to the attending medical physician free of charge throughout the 4 month intervention and 12 month follow up period.

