## Methods and design

### Study design

The design of this study will be a 4-month randomised controlled exercise intervention study (RCT) with a 16 month follow up (Trial registration: ISRCTN65346593). After baseline measurements the voluntary participants will be randomly assigned into the two arms of the study, an aquatic resistance strength training group and a control group. All the outcome measurements will be performed at baseline, after the 4-month intervention and at follow up 12 months after cessation of training.

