#### Daily physical activity

During both the intervention period (0–4 months) and the follow up period (5–16 months) daily physical activity of every subject (excluding pool training) will be recorded using a leisure time physical activity diary. The diary is completed daily and each activity, duration and intensity (1 = low, 2 = moderate or 3 = hard) is recorded. From this data MET-hours per week will be calculated [114,115]. In addition, during the intervention period each subjects’ daily activity will be measured for 3 days using a heart rate monitor (F6 Polar, Polar Oy, Finland), accelerometers (Hookie AM 20, Traxmeet, Finland) and hourly physical activity diaries.

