#### Intervention

Those subjects randomised into the intervention group will participate in 1 hour of aquatic resistance training, three times a week for 4 months, totally 48 training sessions. The intervention will be completed in small groups of 6–8 subjects in a pool heated to 32 degrees with depths 1.3-1.5 m. Aquatic steps will be used to ensure that all subjects will complete the standing exercises at a depth level approximately to their xiphoid bone ±5 cm ensuring weight bearing on the supporting leg of 25-50% of own body weight [41].

Each training session will last approximately 1 hour. The session will consist of three distinct parts; the warm-up (15 minutes), lower limb strengthening program (35 minutes) and cool down (10 minutes), a full description of exercises can be found from Table 1 and Figures 2, 3, 4, 5, 6. Warm up and cool down was planned by a physiotherapist with over 10 years of aquatic therapy experience with patients suffering from musculoskeletal problems (BW), the same therapist will ensure that quality of movement and intensity of the intervention is maintained throughout the training by reviewing the heart rate and perceived exertion by BORG 6–20 scale [116] which are collected after every training session immediately after the main set before the cool down. All sessions will be supervised by 2 experienced physiotherapists, who had been trained to instruct these aquatic programmes and accredited for life-saving before the trial began.

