6-8 and 12	Small/Large	3	14-20	45	30	16-17	30	420-600
9-11 and 13–16 (alternating)	Large	3	14-20	45	30	16-18	30	420-600
	Large	3	12 to 15	30	45	16-18	26	288-360

*PRE = perceived rate of exertion (BORG 6–20).

Weeks 1–2 is an introductory period to allow subjects to become familiar with the movements with sets of 45 seconds duration per leg per set with no resistance i.e. barefoot. Weeks 3–5 will consist of alternate trainings of 30 or 45 seconds with small fins (THERABAND PRODUCTS, The Hygienic Corporation, Akron, OH 44310 USA). Weeks 6–8 will be 3 week period with 45 seconds of work alternating sessions with small aquafins and large resistance boots (Hydro-Tone hydro-boots, Hydro-Tone Fitness Systems, Inc. Orange, CA 92865–2760, USA). Weeks 9–11 and 13–16 will consist of alternate trainings with work of 30 and 45 seconds with large boots. Week 12 will consist of one session barefooted, one with small fins and one with large boots, work duration will be 45 seconds per set. The frontal area of aquafin resistance fins is 0.0181 m^2^ and that of the large resistance boots 0.075 m^2^. In a previous study the drag experienced during seated aquatic knee flexion/extension exercises in healthy women was triple with the large boots compared to the barefoot condition. Additionally, a significant increase in EMG activity was seen with the large boots compared to no boots [117,122].

Intensity of training of every session will be monitored using polar heart rate monitors (F6 or RCX5, Polar Oy, Finland) and perceived rate of exertion (BORG 6–20) [116]. Target training zone will be 60-80% of maximum heart rate according to the Karvonen formula e.g. 60% training limit = (220 – age) x 0.6 and 80% training limit = (220 – age) x 0.8.

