#### Control group

The control group will be asked to maintain normal physical activity during the intervention period. They will be offered two sham contact sessions consisting of 1 hour of light stretching and relaxation during the 4 month period.

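### Adverse-event and session-symptom capture is asymmetric by design, so it can describe tolerability in the training arm but cannot support a between-arm comparison of harms

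*Protocol article*

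**What the plan says.** The protocol article's section Assessment of side effects contains two separate rules.

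- **Adverse events, limited by attribution.** "Adverse effects or health problems attributable to the testing protocol or interventions exercise protocol will be documented and reported".
- **Symptoms, tied to sessions, with no attribution condition.** "Following each individual measurement and training session self-reported knee pain will be assessed using a visual analogue scale", "along with any other physical symptoms such as pain elsewhere than knee, stiffness and general fatigue".

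Other sections fix how often each arm meets the second rule:

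- Intervention: training takes place "three times a week for 4 months, totally 48 training sessions".
- Study design: "All the outcome measurements will be performed at baseline, after the 4-month intervention and at follow up 12 months after cessation of training". This applies to both arms.
- Control group: controls are offered "two sham contact sessions consisting of 1 hour of light stretching and relaxation during the 4 month period". No symptom query is stated for these sessions.

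Some capture is the same in both arms. Under Health status, all subjects report their daily analgesic use for knee pain throughout follow-up, with space for it in the activity diary. WOMAC and KOOS, which include pain domains, are outcome measures at each time point. All subjects have free access to the attending physician for the 4 + 12 months. Under Daily physical activity, covering months 0–4 and 5–16, "daily physical activity of every subject (excluding pool training) will be recorded using a leisure time physical activity diary".

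**The concern.** Unequal opportunity to report produces unequal counts even when the true risks are equal. Here the inequality is built in at two points.

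First, the adverse-event rule asks for attribution before an event is documented. A control has no exercise protocol, so testing is the only route by which her event can qualify. A knee flare, fall or new pain between visits drops out for a control, while the same event in a trained woman can qualify if it is attributed to the exercise.

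Second, the symptom query follows sessions, and nearly all scheduled sessions belong to one arm.

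What is at stake is whether the trial can say anything about harms relative to usual activity. A count of adverse events or symptomatic sessions set out by arm would tend to show an excess with training, caused by the collection schedule alone. There would be no comparable control rate against which to judge it. This cannot be repaired at the analysis stage, because events that were never collected in controls cannot be recovered.

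**Working it through.** **Inputs (all from the protocol article).** Training frequency and number of sessions: Intervention. Length of training: the program runs to week 16 ("Weeks 9–11 and 13–16 will consist of alternate trainings with work of 30 and 45 seconds with large boots", text accompanying Table 2). Measurement time points: Study design (baseline, 4 months, 16 months = 3). Control sessions: Control group (2, offered).

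**Step 1: reproduce the stated number of sessions.** 3 per week × 16 weeks = 48. This agrees with the article.

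**Step 2: scheduled symptom queries per woman over the trial.** Each measurement time point is counted once.

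| Counting rule | Training | Control | Ratio |
|---|---|---|---|
| Sham sessions not queried (as written) | 48 + 3 = 51 | 3 | 17:1 |
| Sham sessions queried (not stated) | 51 | 3 + 2 = 5 | 10.2:1 |
| After baseline only, sham not queried | 48 + 2 = 50 | 2 | 25:1 |

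**Step 3: sensitivity to how measurements are counted.** The wording could mean a query after every individual test. With k queries per time point, the counts are 48 + 3k against 3k:

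- k = 1: 51 against 3 (17:1)
- k = 2: 54 against 6 (9:1)
- k = 5: 63 against 15 (4.2:1)

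The ratio over the whole trial falls as k rises. In the interval between the baseline and 4-month visits k plays no part, and the count stays at 48 against 0 to 2.

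**Step 4: illustration under equal true risk.** Assume that each query has the same probability p of yielding a report in both arms, independently. The values of p are assumptions; the article gives none. P(at least one report) = 1 − (1 − p)^n.

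| p (assumed) | Training, n = 51 | Control, n = 3 | Control, n = 5 |
|---|---|---|---|
| 0.01 | 40.1% | 3.0% | 4.9% |
| 0.02 | 64.3% | 5.9% | 9.6% |
| 0.05 | 92.7% | 14.3% | 22.6% |
| 0.10 | 99.5% | 27.1% | 41.0% |

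A large apparent excess appears in the training arm with no true difference.

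**Step 5: what the symmetric sources cover.**

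- *Daily analgesic record:* knee pain treated with drugs. It misses flares managed without drugs, pain elsewhere, stiffness, fatigue and injuries.
- *WOMAC/KOOS:* knee status at three time points. They can miss a flare that resolves between visits.
- *Physician access:* available to everyone but not described as a data source. An event seen there would still have to meet the attribution rule to be documented as an adverse effect.

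**The case against.** The strongest counter-argument is that the article announces no between-arm comparison of adverse events or of the session VAS. It says only that events will be documented and reported. A VAS taken straight after vigorous exercise measures acute tolerability, for which controls have no natural counterpart. The detail of adverse-event handling also normally sits in the full protocol, which is not shown. All of this stands. The bias is conditional on a comparison being made, and only the stated collection rules can be criticised.

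Several stronger readings are tempting, and the document does not support them:

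- *That knee-pain reports are also filtered by attribution.* They are not. The condition governs adverse effects and health problems; the VAS and symptom query carry no such condition.
- *That controls have almost no chance to report, or that background knee pain is never measured.* Controls are queried at measurement sessions. Both arms also have the daily analgesic record, WOMAC/KOOS and physician access. The analgesic record in particular is a daily, knee-specific proxy that is equal between arms.
- *That attribution is judged with knowledge of the arm.* The section does not say who judges attribution or on what information.
- *That the trial will publish a biased safety comparison.* None is announced.

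The illustration in Step 4 has limits as well. No flare event is defined, the VAS is continuous, and one common p for post-exercise and visit queries is a simplification. It shows the direction and possible scale of the artefact and is not a forecast.

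The asymmetry itself survives these points. It follows from two rules that the article states and does not depend on anything it leaves out. The symmetric sources cover knee pain only in part, and they do not systematically cover pain elsewhere or injuries, although the article regards symptoms beyond the knee as worth asking about.

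**Conclusion.** The point holds in a limited form. Adverse-event capture depends on attribution to testing or exercise, which largely excludes control-arm events between visits. Scheduled symptom queries run at 51 against 3 per woman if each measurement time point counts once, or 51 against 5 if sham sessions are queried. The whole-trial ratio is smaller if each test at a visit triggers its own query, but the imbalance between the baseline and 4-month visits remains 48 against 0 to 2.

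The data as collected can describe tolerability in the training arm. They cannot support a statement that training raises or lowers harms compared with the control condition. The counts assume full attendance at the planned sessions. The primary MRI outcomes, and the knee-pain outcomes measured by questionnaire in both arms, are unaffected.

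**What to change.** 1. Add one line for knee symptoms and any other health problem to the physical activity diary that every subject already completes daily to month 16, next to the existing space for analgesic use.
2. Reword the first rule under Assessment of side effects so that adverse events are recorded in both arms irrespective of attribution, with attribution kept as a separate field.
3. State that any between-arm comparison of harms will rest on the diary line and these records.
4. State that the after-session VAS and symptom query will be reported only as tolerability within the training arm.

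The cost is one diary line, a few sentences of protocol text, and slightly more diary burden and data entry. No extra visit or contact is needed, and neither the intervention nor the primary outcomes change.

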#### Statistical analysis

All analyses will be based on both intention-to-treat and dose related principles. Statistical analyses will be performed using statistical software (Stata, release 12.1, StataCorp, College Station, Texas and SPSS Version 19, IBM Corporation).

## Discussion

This paper describes the rationale and design of a randomised control trial investigating the effect a progressive aquatic resistance training program will have on patellofemoral and tibiofemoral cartilage, properties of bone and body composition and physical function in post-menopausal women with mild knee osteoarthritis.

Exercise is one of the main non-pharmaceutical treatments recommended in the management of lower limb OA [24-26,28,29]. It is presumed that training in an aquatic environment has benefits for persons suffering from lower limb OA, however exact content and intensity of optimal training remain unclear [22]. For persons with knee and/or hip OA there is strong evidence to suggest aquatic exercise can cause a small but significant reduction in pain [30,33,34,36,38,123-127], improves self-assessed and measured function with a small to moderate effect size [33-36,38,123-125,127-130]. In addition, there is moderate evidence to show that aquatic exercise can cause a small but significant improvement in aerobic fitness [33,35,127,129,131]. Further there is limited data to suggest aquatic exercise can increase lower limb strength [33-39] and improve balance and decrease risk of falling [36,39,40]. Intensities of interventions in previously studies may not have been high enough to produce large changes in muscle strength and cardiovascular fitness but reporting of exercise programs used are in most cases incomplete. There are few studies investigating the effect of a progressive resistance program using specifically designed resistance equipment to manage symptoms associated with knee OA even though there is accumulating evidence to suggest it can be effective in improving neuromuscular function [117,118,120-122]. Also, there is some evidence to suggest water based exercise can either maintain [132] or slightly improve the properties of bone as measured with DXA [133]. However these are of low quality evidence and further research is required to validate the findings.

Both dGEMRIC [63,134] and T2 relaxation MRI [7,72,135] can distinguish between normal and OA cartilage. These techniques have been shown to be sensitive enough to demonstrate acute changes in human cartilage dGEMRIC [42,67] and T2-relaxation times [42,136]. These methods are therefore suitable for use in our study, and it is known that correct biomechanical loading of cartilage is important in maintaining cartilage health whereas obesity and trauma are risk factors for the development of OA [1]. Although there is evidence to show that biochemical characteristics of cartilage can be negatively affected with changes after periods of joint immobilization [137,138] and non-weight bearing [136]. No evidence exists to show the impact of an intensive non-impact exercise on cartilage.

As far as we know there have been no publications investigating the effect of aquatic exercise on cartilage and properties of bone in persons with knee OA. The aim of this study is to use repetitive aquatic resistance program with high intensity and repetition to discover what effects non-impact training has on knee cartilage, properties of bone and physical function. The information gained will help improve our understanding of the effects of exercise on the biochemical properties of cartilage and improve prescription of aquatic exercises in the management of OA.

## Abbreviations

OA: Osteoarthritis; ROM: Range of Motion; pQCT: Peripheral quantitative computed tomography; DXA: Dual-energy X-ray absorption; WOMAC: Western Ontario and McMaster Universities Osteoarthritis Index; KOOS: Knees injury and Osteoarthritis Outcome Score; CV: Coefficient of Variation; VAS: Visual Analogue Scale; RPE: Rate of Perceived Exertion; MRI: Magnetic Resonance Imaging; dGEMRIC: Delayed Gadolinium-Enhance Magnetic Resonance Imaging of Cartilage; FOV: Field of View; TR: Repetition Time; TE: Echo Times; ETL: Echo Train Length; GAG: Glycosaminoglycan; BMD: Bone Mineral Density; BSI: Bone Strength Index; BMC: Bone Mineral Content; ToD: Total Density; TrD: Trabecular density; ToA: Total Area; TrA: Trabecular Area; aBMD: Areal Bone Mineral Density; BMC: Bone Mineral Content; AHA: Advance Hip structure Analysis; HAL: Hip Axis Length; CSA: Cross Sectional Area; CSMI: Cross Sectional Moment of Inertia (CSMI); FSI: Femoral neck Strength Index; BMI: Body Mass Index; CMJ: Counter Movement Jump; ECG: Echocardiogram.
